## Abstract

**Background:**

Patterns of diagnosis and management for men diagnosed with prostate cancer in Queensland, Australia, have not yet been systematically documented and so assumptions of equity are untested. This longitudinal study investigates the association between prostate cancer diagnostic and treatment outcomes and key area-level characteristics and individual-level demographic, clinical and psychosocial factors.

**Methods/Design:**

A total of 1064 men diagnosed with prostate cancer between February 2005 and July 2007 were recruited through hospital-based urology outpatient clinics and private practices in the centres of Brisbane, Townsville and Mackay (82% of those referred). Additional clinical and diagnostic information for all 6609 men diagnosed with prostate cancer in Queensland during the study period was obtained via the population-based Queensland Cancer Registry.

Respondent data are collected using telephone and self-administered questionnaires at pre-treatment and at 2 months, 6 months, 12 months, 24 months, 36 months, 48 months and 60 months post-treatment. Assessments include demographics, medical history, patterns of care, disease and treatment characteristics together with outcomes associated with prostate cancer, as well as information about quality of life and psychological adjustment. Complementary detailed treatment information is abstracted from participants' medical records held in hospitals and private treatment facilities and collated with health service utilisation data obtained from Medicare Australia. Information about the characteristics of geographical areas is being obtained from data custodians such as the Australian Bureau of Statistics. Geo-coding and spatial technology will be used to calculate road travel distances from patients' residences to treatment centres. Analyses will be conducted using standard statistical methods along with multilevel regression models including individual and area-level components.

**Conclusions:**

Information about the diagnostic and treatment patterns of men diagnosed with prostate cancer is crucial for rational planning and development of health delivery and supportive care services to ensure equitable access to health services, regardless of geographical location and individual characteristics.

This study is a secondary outcome of the randomised controlled trial registered with the Australian New Zealand Clinical Trials Registry (ACTRN12607000233426)

## Background

Internationally, prostate cancer is the second most common cancer diagnosed among men worldwide (12% of all cancers) and the 6th most common cause of cancer-related deaths [1]. Prostate cancer is particularly prevalent in developed countries such as the United States, Scandinavian countries, Canada and Australia, with about a six-fold difference between high-incidence and low-incidence countries[2]. Among Australian males in 2010, prostate cancer is expected to have the second highest cancer-related disease burden, measured by disability-adjusted life years (DALYs), behind lung cancer [3].

Based on autopsy studies, substantial proportions of men have histological prostate cancer that doesn't cause symptoms or death [4,5]. Since the introduction of PSA testing, increasing numbers of these indolent prostate cancers are now being diagnosed [6]. As such, many of the prostate cancers being diagnosed will have little impact on a man's health even in the absence of treatment [7] and that treatment may in fact be harmful as it may carry significant side effects with no potential benefit. However many prostate cancers do have the potential to metastasise and cause death. Worldwide, there were nearly 260,000 deaths caused by prostate cancer in 2008, with 53% of these being in developed regions[8]. We have shown previously that a diagnosis of prostate cancer has greater implications for men diagnosed at a young age, with these men being more likely to die prematurely[9]. Unfortunately it is not currently possible to differentiate the indolent cancers from those that have the potential to metastasise before biopsy, thus making the important decision of whether to be screened and subsequent treatment decisions potentially complex and distressing.

For localised prostate cancer, potentially curative treatment options include surgery through radical prostatectomy and radiation therapy (external beam and brachytherapy). While these surgical or radiation treatments may increase the chance of cure, they are associated with a significant risk of impotence, and less commonly urinary incontinence and bowel problems. The prevalence and type of side-effects vary for different treatment types[10]. Another treatment option is active surveillance, in which treatment is initially deferred, then initiated if the disease progresses. This differs from "watchful waiting" in which medical treatment is reserved until symptoms become evident, thus potentially missing the opportunity for cure. In contrast close observation maintains the likelihood of cure by intervening before symptoms present.

The contrasting initial results recently published from two large-scale prostate cancer screening trials in the United States [11] and Europe [12] highlight the complexity of issues surrounding the provision of diagnostic and treatment services for prostate cancer. In the presence of already high PSA testing, the United States study suggested that organised PSA population screening programs are likely to result in over-diagnosis and over-treatment with little reduction in mortality. Conversely, in Europe where the prevalence of asymptomatic detection is low, there is greater potential for screening programs to reduce the number of advanced prostate cancers and deaths from prostate cancer. A sub-study conducted in Göteborg, Sweden, a country with a low prevalence of PSA testing (3%)[13] found that using an intention to treat analysis PSA testing almost halved the risk of death from prostate cancer. A major difference between this study and its two larger international predecessors is its more appropriate duration of follow-up viz. 14 years.

Internationally, there is substantial evidence that socio-demographic factors, such as age, ethnicity, location of residence and income are associated with prostate cancer outcomes extending from the likelihood of a man having a PSA test to differences in prostate cancer management [2,14-18]. In Australia [15] there has been a statistically significant and increasing excess of prostate cancer mortality among men in regional and rural areas compared with those living in capital cities. This mortality excess was accompanied by lower rates of radical prostatectomy and PSA testing in rural and regional Australia, and was in spite of lower incidence rates of prostate cancer.

At present, the patterns of care for men in Queensland, Australia, are not documented in any systematic way. For example, for men diagnosed with prostate cancer, we currently do not know which medical treatments they receive, what factors are associated with different choices, nor the morbidity and mortality risks associated with these different treatments in their settings. Since this information is needed for the planning and development of health delivery and supportive care services and to ensure equitable access to health services, this longitudinal study of men diagnosed with prostate cancer in Queensland was undertaken.

### Study Aims

Utilising a longitudinal study design and recruiting men immediately after their initial diagnosis, this study aims to obtain information about their initial symptoms and diagnosis, and then prospectively follow them during subsequent management to identify their pathways to care and subsequent outcomes. Specifically it aims to:

1. Document the current diagnostic and treatment patterns for men with prostate cancer, in Queensland, Australia;

2. Investigate the determinants of area-level and individual-level variation in diagnostic and treatment pathways;

3. Investigate the determinants of area-level and individual-level variation in clinical, psychosocial and survival outcomes following treatment for prostate cancer;

4. Identify inequalities in diagnostic and treatment pathways, with a view to translating that information into health policy and practice decision-making.

## Methods/Design

### Study Design

This is a descriptive, longitudinal epidemiological study, in which is embedded a randomised controlled trial of a decision support intervention for men with localised prostate cancer. The descriptive epidemiology component is a secondary outcome of the randomised controlled trial [19] and has been registered with the Australian New Zealand Clinical Trials Registry (registration number ACTRN12607000233426).

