##### Primary Outcome Measures

Diagnostic pathway: a description of events and time line from first noticing symptoms or presenting to a medical practitioner to the definitive diagnosis. This includes the diagnostic interval, defined as the time between the initial doctor's consultation for reasons that led to the prostate cancer diagnosis, and the date of definitive diagnosis.

Treatment pathway: a description of events and time line from the definitive diagnosis to 6 months post the commencement of primary treatment. This includes the treatment interval, which is the time between the definitive diagnosis and the commencement of primary treatment for the prostate cancer.

Treatment details: a description of the type, duration and frequency of all treatments received by the participant between diagnosis and 6 months after the commencement of primary treatment. Primary treatment is considered the first most invasive treatment undergone by the participant and is generally radical prostatectomy or radiation therapy (either external beam radiotherapy or brachytherapy). For participants who chose watchful waiting or active surveillance, date of treatment is considered as the date the treatment decision is made.

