### Statistical analysis

Statistical analyses for this study will reflect the sampling design, the data collection process, and the research objectives as stated previously. Due to the typically highly skewed distributions of time to diagnosis or treatment, standard methods for transforming the time intervals such as the geometric mean or comparing median times, will be used in the analyses. Crude and adjusted logistic and multinomial regression analyses of dichotomous and ordinal outcomes respectively, will be used to assess the contribution that independent factors have on men's choice of treatment. We will also investigate the representativeness of the study cohort compared to the rest of the men diagnosed with prostate cancer by comparing the distributions of those clinical and demographic variables collected from the Queensland Cancer Registry.

Previous studies looking at patterns of diagnosis and treatment have focussed on the individual-level data, or ecological studies. In order to appropriately investigate whether the observed patterns are due to the characteristics of the cancer patients themselves, or the characteristics of the geographical areas in which the individuals live, it is important to be able to quantify the variation between areas in terms of their diagnostic and treatment profiles. Thus using a multilevel analytical design we can then determine whether the observed variation is due to the clustering of individuals (i.e. a composition effect) or the environmental characteristics of the areas (i.e. a context effect).

We have previously described the advantages of incorporating a multilevel perspective [32]. We will use multilevel models to assess whether geographic remoteness and area-level disadvantage were associated with prostate cancer outcomes after controlling for individual-level socio-demographic characteristics. These models will be fitted using MLwiN version 2.15 (University of Bristol, United Kingdom).

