There will be three stages in the model building process. The first is the null model that including individuals (level 1) nested in SLAs (level 2), there are no individual- or area-level variables in the fixed part of this model. If there is a significant SLA-level random term (indicated using Wald chi-square) then this is evidence supporting significant between-SLA variation in the prostate cancer outcome. Second, the null model will be extended by including individual-level factors (patient characteristics, disease stage, co-morbidity, and access to health care and treatment services) as fixed effects. This will inform us as to how much of the area-variation in prostate cancer outcomes is due to these individual-level (compositional) factors, and also assess the contribution of each individual-level factor. Thirdly, the area-level measures such as geographic remoteness and area socioeconomic disadvantage will be included in the model as fixed effects, to quantify how much of the area-variation in prostate cancer outcomes is due to these factors (independent of individual-level factors). Subsequent models will also consider the cross-level interactions between the individual-level and area-level factors.

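### The cohort contains a randomised decision-support trial, but the stated models and the Aim 1 treatment description do not account for allocation

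*Protocol article*

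**What the plan says.** Under Study Design, the article states that this is a descriptive cohort "in which is embedded a randomised controlled trial of a decision support intervention for men with localised prostate cancer", and adds: "The descriptive epidemiology component is a secondary outcome of the randomised controlled trial". The described cohort therefore includes the trial's participants.

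The first item under Study Aims is to "Document the current diagnostic and treatment patterns for men with prostate cancer, in Queensland, Australia". The same section says that men are recruited straight after diagnosis, and the questionnaire section places the first assessment before treatment. Primary Outcome Measures includes the type of treatment and the treatment interval, defined as "the time between the definitive diagnosis and the commencement of primary treatment for the prostate cancer". For watchful waiting and active surveillance, the treatment date is the date of the decision.

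Under Statistical analysis, crude and adjusted regressions "will be used to assess the contribution that independent factors have on men's choice of treatment". The multilevel models ask whether remoteness and area disadvantage are "associated with prostate cancer outcomes after controlling for individual-level socio-demographic characteristics". The second stage of model building enters "individual-level factors (patient characteristics, disease stage, co-morbidity, and access to health care and treatment services) as fixed effects". The third stage adds area-level measures, and later models add cross-level interactions. Allocation is not mentioned at any of these points.

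**The concern.** Decision support is directed at the treatment decision, and the treatment decision is what much of this study describes and models. If the intervention changes what men choose, or how long they take to choose, the whole-cohort figures blend ordinary practice with the result of an experiment. They would then be reported as current patterns of care in Queensland and, under Aim 4, used to inform policy.

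Two features make this worth settling in advance. First, balance between arms does not protect a descriptive estimate, because a proportion over all men carries the intervention effect in proportion to the share exposed. Second, eligibility for the trial depends on disease stage, which is itself a model covariate. Exposure can occur among localised men and not among others, so the stage coefficient would absorb part of any effect.

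The planned comparison of the cohort with the 5545 non-participants cannot reveal this. It uses demographic, geographical, clinical and diagnostic registry variables, and similarity on those says nothing about whether treatment choices were altered.

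Psychosocial outcomes (Aim 3) are open to the same question: the article takes their measures from the publication it also cites for the trial.

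**Working it through.** **Inputs from the article.** Cohort size 1064. Planned subgroup contrast: 500 men per group, 9 points, 80% power, two-sided 5%, pooled variance.

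**Inputs assumed, because the text does not give them.** Share of the cohort randomised, f = 0.5 to 0.9. Allocation 1:1. Effect of decision support on the proportion choosing a given treatment, d = 0, 5 or 10 points (up to 15 where stated). Proportions near 50%.

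**The plan's own figure.** Take 50% v 59% with n = 500 per group. The mean proportion is 0.545.

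- z = [0.09 × √500 − 1.96 × √(2 × 0.545 × 0.455)] / √(0.50 × 0.50 + 0.59 × 0.41) = (2.012 − 1.380) / 0.701 = 0.90
- Power = 81.6%

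The stated 80% reproduces. The point made here does not rest on it, but the 9 points give a scale for what follows.

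**Sampling error of an Aim 1 proportion.** 1.96 × √(0.25 / 1064) = 3.0 points.

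**Shift in a whole-cohort proportion.** Shift = f × 0.5 × d. The last column is the half-width of an estimate that drops the intervention arm, gives controls weight 2 to stand for all randomised men, and gives non-randomised men weight 1. Its variance multiplier is 0.5f × 4 + (1 − f) = 1 + f, so the half-width is 3.0 × √(1 + f).

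| f | Share exposed | Shift, d = 0 | Shift, d = 5 | Shift, d = 10 | Half-width without intervention arm |
|---|---|---|---|---|---|
| 0.5 | 0.25 | 0 | 1.25 | 2.5 | 3.7 |
| 0.6 | 0.30 | 0 | 1.5 | 3.0 | 3.8 |
| 0.8 | 0.40 | 0 | 2.0 | 4.0 | 4.0 |
| 0.9 | 0.45 | 0 | 2.25 | 4.5 | 4.1 |

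**Localised-versus-advanced contrast.** If all localised men are randomised 1:1, half are exposed, and no advanced man is. The contrast then absorbs 0.5 × d, which is 2.5 to 5 points for d = 5 to 10. It absorbs proportionately less if only some localised men are randomised.

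**Area and other patient contrasts.** Two routes to bias remain.

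- *The subgroups differ in the share randomised.* Bias = difference in f × 0.5 × d. With a difference of 0.1 to 0.2 and d = 5 to 15, this runs from 0.1 × 0.5 × 5 = 0.25 to 0.2 × 0.5 × 15 = 1.5 points.
- *Chance imbalance of arms between two subgroups of 500.* The 95% bound is 1.96 × √(0.5 / (500f)) × f × d. For d = 10 this is 0.44 points at f = 0.5 and 0.59 points at f = 0.9.

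Both are small beside the 9 points for which the study was sized.

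**Diagnostic interval.** It ends at the definitive diagnosis, and men were recruited after that, so allocation cannot affect it.

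**The case against.** The strongest reply is that silence is not exclusion. The article speaks of independent factors without listing them, describes the individual-level block by broad domains, and says that analyses will reflect the sampling design and data collection. A condensed article may leave exact covariates to the full protocol or analysis plan, which are not at hand. A reader might infer from the article that allocation has been ruled out of every model. The text does not support that: it names model terms and allocation is not among them, but nothing forbids its use.

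A reader might also infer that the described patterns are known to be distorted. The article does not show this either. It gives no effect size, number randomised, allocation ratio or comparator, and does not say that decision support is meant to change which treatment men choose. It might improve the quality of the decision, or reduce distress, and leave treatment proportions as they were.

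A third tempting inference is that the area and inequality findings are confounded. Random allocation should be roughly balanced over areas and patient factors, and the figures above bear this out, so that reading fails.

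Finally, making the estimate without the intervention arm the main one would impose a certain loss of precision to avoid a bias that may be zero. This stands, and it is why that estimate belongs in a sensitivity analysis.

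What survives is narrower. The article discloses the trial, sets out its covariate blocks and modelling stages, and provides no handling for an intervention that acts on a primary outcome.

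**Conclusion.** The point holds as a low-cost improvement to the stated analysis; it is not a demonstrated bias. As written, the plan would fold any effect of decision support into the Aim 1 treatment proportions and intervals, the post-treatment psychosocial results and the localised-versus-advanced contrast.

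Under the assumed ranges, a whole-cohort proportion shifts by 1.25 to 4.5 points and the stage contrast by 2.5 to 5 points. Both are zero if the intervention has no effect. The first range runs from below to above the 3.0-point half-width, so the effect could matter, and the stated analysis would not show whether it does.

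These sizes rest on an assumed share randomised, ratio and effect; only the cohort size comes from the article. The conclusion does not extend to area contrasts, to patient contrasts other than stage, or to the diagnostic interval. Handling of allocation in documents not at hand cannot be excluded.

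**What to change.** 1. Add a three-level allocation term (intervention, control, not randomised) as a fixed effect in the models of treatment choice, treatment interval and post-treatment psychosocial outcome. A two-level indicator that pools controls with non-randomised men would merge groups that may differ in stage or in willingness to join the trial. If every localised man was randomised, the non-randomised level coincides with advanced disease. Stage plus an intervention indicator then carries the same information.
2. Report Aim 1 treatment patterns and treatment intervals by allocation group, beside the full-cohort figures.
3. Add a sensitivity estimate that excludes the intervention arm. Reweight controls to stand for all randomised men only, and keep non-randomised men at weight one. Weighting controls up to all localised men would count any non-randomised localised men twice.
4. Leave the diagnostic-interval analyses unchanged.

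The trial already holds the allocation data, so no new collection is needed. The cost is two extra parameters per model, some additional tabulation, and a wider interval for the sensitivity estimate: about 3.8 to 4.0 points instead of 3.0 if 60-80% of the cohort was randomised 1:1. The full-cohort estimate keeps its precision.

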### Ethical Clearance

The full study, including documentation of the patterns of diagnosis and treatment, has been approved by the Queensland University of Technology Human Research Ethics Committee, in addition to the ethics committees of ten public hospitals in Queensland. The collection of Medicare data has been approved by Medicare Australia and access to data from the Queensland Cancer Registry was approved by Queensland Health.

### Setting

Men diagnosed with prostate cancer in Queensland (Australia) between February 2005 and July 2007 (inclusive) are eligible for this study. As the second largest area of the Australian states and territories, Queensland has the third highest population of any state (4.4 million in 2009) and is the most decentralised [20]. Recruitment is centred on the two major tertiary treatment centres for prostate cancer in Queensland; the greater Brisbane and Townsville areas.

### Study areas

Participants were ascertained through urology outpatient clinics in the Greenslopes Private, Royal Brisbane, Mater Adults, Princess Alexandra, Ipswich, QEII, Redlands, and Redcliffe Hospitals in Brisbane (and surrounds) and through the Townsville General Hospital and Mackay Base Hospital. Private patients were ascertained through the private practices of Urologists in Brisbane (and surrounds), Townsville and Mackay.

